## Abstract

**Background:**

In Germany, the proportion of people with chronic diseases and multimorbidity is increasing. To counteract the emergence and worsening of age-related conditions, there is a need for preventive care structures and measures. The preventive services that are financed by statutory health insurance (SHI; eg, vaccinations, cancer screening) are only used by part of the German population. There are no current findings about the utilization of these services by older adults in the eastern German federal state of Saxony-Anhalt, which is particularly strongly affected by demographic change.

**Objective:**

The aim of this study is to investigate the actual utilization and determinants of, reasons for, and barriers to utilization of preventive services financed by the SHI in Saxony-Anhalt in the 55-plus age group.

**Methods:**

In this study, a convergent mixed methods design is used. The actual use of preventive services will be shown by means of (1) a claims data analysis looking at data on statutory outpatient medical care from both the Central Research Institute of Ambulatory Health Care in Germany (Zi) and the Association of Statutory Health Insurance Dentists in Saxony-Anhalt (KZV LSA). The determinants, attitudes, and behaviors associated with use will be analyzed through (2) a cross-sectional survey as well as (3) qualitative data from semistructured interviews with residents of Saxony-Anhalt and from focus group discussions with physicians. (4) A stock take and systematic evaluation of digitally available informational material on colorectal cancer screening, by way of example, provides an insight into the information available as well as its quality. The conceptual framework of the study is the behavioral model of health services use by Andersen et al (last modified in 2014).

**Results:**

(1) The Zi and KZV LSA are currently preparing the requested claims data. (2) The survey was carried out from April 2021 to June 2021 in 2 urban and 2 rural municipalities (encompassing a small town and surrounding area) in Saxony-Anhalt. In total, 3665 people were contacted, with a response rate of 25.84% (n=954). (3) For the semistructured interviews, 18 participants from the 4 different study regions were recruited in the same period. A total of 4 general practitioners and 3 medical specialists participated in 2 focus group discussions. (4) For the systematic evaluation of existing informational material on colorectal cancer screening, 37 different informational materials were identified on the websites of 16 health care actors.

**Conclusions:**

This study will provide current and reliable data on the use of preventive services in the 55-plus age group in Saxony-Anhalt. It will yield insights into the determinants, reasons, and barriers associated with their utilization. The results will reveal the potential for preventive measures and enable concrete recommendations for action for the target population of the study.

**Trial Registration:**

German Clinical Trials Register DRKS00024059; https://www.drks.de/drks_web/navigate.do?navigationId=trial.HTML&TRIAL_ID=DRKS00024059

**International Registered Report Identifier (IRRID):**

DERR1-10.2196/33512

## Introduction

### Background

The eastern German federal state Saxony-Anhalt (part of the former German Democratic Republic) is strongly affected by demographic change. In 2019, the proportion of the population of Saxony-Anhalt aged 65 years and older was approximately 27% of the total population [1]. The aging of the population is accompanied by an increasing need for care, which is leading to growing structural challenges in medical care. For instance, the density of physicians in Saxony-Anhalt in 2020 was 197.9 physicians per 100,000 inhabitants. In comparison, the density of physicians in the western German federal state of Bavaria was 221.5 physicians per 100,000 inhabitants [2]. According to the German Index of Socioeconomic Deprivation, developed by the Robert Koch Institute, Saxony-Anhalt has a comparatively high level of socioeconomic deprivation. Empirical evidence has shown that this is associated with negative health impacts such as an accumulation of health risks. Moreover, the prevalence of individual risk factors (eg, smoking, obesity) is higher in Saxony-Anhalt than the national average [3].

As in many developed countries, in Germany, the proportion of people with chronic diseases and multimorbidity is rising due to increasing life expectancy and advances in medical technology [4]. Furthermore, from 1959 to 1968, there were very high birth rates in East Germany. The children born in this period, the so-called “baby boomers,” currently constitute the largest age group in Germany [5]. The first baby boomers will leave the labor force in 2025 and pass the aforementioned threshold of 65 years of age. It is expected that there will be an increase in chronic diseases in this age group in the coming years [6]. Cardiovascular diseases and cancer, which can be influenced by preventive measures, mainly cause the burden of disease in Germany [4]. According to hospital diagnosis–related group statistics, cardiovascular diseases caused 8.8% of all full inpatient hospital cases in 2019. In Saxony-Anhalt, the full inpatient hospitalization rate is 17.4% higher than the national average [7].

Preventive care structures and measures are needed to counteract the development and deterioration of age-associated diseases and to maintain and strengthen health, independence, and participation in social life into old age. Therefore, in addition to the avoidance of disease risks, prevention in old age pursues the goal of strengthening physical, psychological, and social resources, also in the case of existing health-related and functional restrictions [8]. In this context, primary and secondary preventive measures are particularly relevant. In Germany, public health is the responsibility of the federal states and covers, for example, the surveillance of infectious diseases. Some public health services, such as medical and dental check-ups, vaccinations, and cancer screening are financed by statutory health insurance (SHI), which insures approximately 87% of the German population. In Germany, all citizens must have either statutory or private health insurance, whereby a number of criteria regulates who is insured in which system [9]. Further details about the German health system and its financing were published in [9,10]. Details on the scope, eligible populations, and examination intervals of SHI-financed preventive services can be found in [11,12]. In 2015, the “Act to Strengthen Health Promotion and Disease Prevention” (“Gesetz zur Stärkung der Gesundheitsförderung und der Prävention”) was passed by the German legislature. It aims particularly to strengthen health promotion in living environments (settings). Moreover, it contains regulations to strengthen the vaccination system and to further develop health and early detection examinations.

The effectiveness of preventive services depends on the extent of their use. In Germany, preventive services have been underutilized. In 2018, only about 35% of the German population aged 65 years and older had been vaccinated against seasonal influenza. This is below the European Union average of 44% [4]. In comparison, in 2018/2019, the vaccination coverage rate for seasonal influenza in Saxony-Anhalt was 59% among people aged 60 years and older, which is above the national average [13]. The target vaccination coverage rate defined by the World Health Organization for older people is at least 75%. This is not nearly achieved, neither nationwide nor in Saxony-Anhalt. The cancer screening tests offered (eg, breast cancer screening) are only used by part of the eligible population, but there is a mixed picture in terms of utilization rates depending on the screening program [4]. It should be noted that cancer screening can also cause harm (eg, overdiagnosis, false-positive results). Therefore, since 2013, Germany's health policy aims to increase informed decision making for or against screening [14]. Several studies have shown that numerous determinants and barriers influence the utilization of preventive services in Germany. The level of utilization differs according to social status, sex, age, residential region (eastern and western Germany), health status, and health-related behavior, among other factors [15-18].

Based on the initial situation described in the previous paragraphs, it can be assumed that, in the federal state Saxony-Anhalt, there are comparatively pronounced determinants that are negatively associated with the utilization of preventive services. However, for Saxony-Anhalt’s older population, there are no current, representative findings on the utilization of these services and the associated influencing factors.

### Objectives of the Study

In the mixed methods study, “Prevention in old-age Saxony-Anhalt” (“Prävention im Alter Sachsen-Anhalt” [PrimA LSA]), we examine the actual utilization and the determinants, reasons, and barriers influencing the use of preventive services in Saxony-Anhalt in the 55-plus age group. The aim is to identify further potential for prevention in the aging population and to derive recommendations for measures leading to needs-driven improvement or further development of preventive services and their utilization. Our focus is on medical services for primary prevention (vaccinations) and secondary prevention (cancer screening, medical and dental check-ups).

## Methods

### Overview of the Study Design

The target population of the study consists of residents aged 55 years and older living in the eastern German federal state of Saxony-Anhalt. By means of an analysis of claims data—the billing data from the SHI—the actual utilization of preventive services in the target population will be shown. The determinants, attitudes, and behaviors associated with utilization will be analyzed using a survey as well as qualitative data from semistructured interviews with residents of Saxony-Anhalt and from focus group discussions with physicians. A search for and systematic evaluation of existing informational material on the applicable preventive services provide insight into the information available and its quality. In addition, it enables further development of existing informational material and an analysis of the relevant health care actors. Figure 1 provides an overview of the study design and its methodological strands.

In this study, a convergent mixed methods design is used (Figure 2). The qualitative and quantitative data are collected simultaneously with equal priority. First, the data will be analyzed separately and will then be merged and interpreted together. This ensures a comprehensive and complementary understanding of the investigated research topic [19].

**Figure 1 figure1:**
[figure not shown]
Overview of the study design. GP: general practitioner.

**Figure 2 figure2:**

Flowchart of the convergent mixed methods design of the study. Modified from [19].

Our study is accompanied and supported by regional cooperation partners, like nonstatutory welfare institutions, the Association of Statutory Health Insurance Physicians in Saxony-Anhalt (Kassenärztliche Vereinigung Sachsen-Anhalt [KVSA]) and the Association of Statutory Health Insurance Dentists in Saxony-Anhalt (Kassenzahnärztliche Vereinigung Sachsen-Anhalt [KZV LSA]). In regular meetings, we discuss the current state of the study as well as further steps in order to ensure the transfer of research to practice. In addition, the study is part of the academic training of specialists in the field of prevention and health promotion.

The conceptual framework of the study is the behavioral model of health services use by Andersen et al (last modified in 2014) [20], which enables the identification of factors influencing the extent to which preventive services are utilized. It encompasses individual and contextual characteristics, the health behavior of individuals, as well as the outcomes of the use of health services. At the level of individual and contextual characteristics, the model distinguishes predisposing (eg, sex, age), enabling (eg, health insurance status, accessibility of health care facilities), and need factors (eg, existing risk factors) [20]. In line with Andersen et al [20] and other previous studies that examined the determinants, reasons, and barriers to the use of preventive services [15-18], we assume that the utilization depends especially on the aforementioned 3 factors. The results of the qualitative and quantitative parts of the study will be analyzed and related to each other based on the dimensions of the model by Andersen et al [20].

### Claims Data Analysis

Current and reliable data on the actual use of preventive services are indispensable for target group–specific communication about these services as well as for the evaluation and further development of existing recommendations and programs (eg, organized cancer screening programs). For this reason, aggregated claims data from statutory outpatient health care from the Central Research Institute for Ambulatory Health Care in Germany (Zi) and the KVSA will be analyzed in the study. These data provide information about services billed to the SHI for all people aged 55 years and older who are insured under the SHI scheme in the federal state of Saxony-Anhalt. For legal or technical reasons, both institutions keep the data for different periods.

The Zi has national statutory health care billing and prescription data from outpatient care that are submitted by all 17 associations of SHI physicians in Germany [21]. Within the framework of our analysis, we will consider the following groups of services: consultations and examinations for early cancer detection, medical check-ups as well as the vaccinations recommended by the German Standing Committee on Vaccination (STIKO) for the relevant age group (eg, influenza, streptococcus pneumoniae, herpes zoster) [22]. The utilization rates will be calculated as the number of insured people who have made use of a certain service at least once within a defined reporting period, divided by the population eligible for the respective service among those with SHI. The key epidemiological figures will be shown for the entire target population and stratified according to age group (5-year age brackets up to age 95 years and older), sex, region, and reporting year as well as other characteristics, for example the existence of chronic diseases or diseases with a vaccination indication (eg, cardiovascular diseases, diabetes) [22]. The utilization will be presented chronologically from 2011 to 2020. Since the Zi has national claims data at its disposal, the utilization rate in Saxony-Anhalt will be compared with the rate for the entire German federal territory. Regional differences in Saxony-Anhalt will be examined at the district and urban district levels (German: *Landkreis* and *kreisfreie Stadt*, respectively).

In order to obtain additional empirical information about the preventive dental care of older residents in Saxony-Anhalt, data from the KZV LSA will be analyzed. Here, we will consider the utilization of dental check-ups, the costs of which are covered by the SHI once in every calendar half year, as well as visits to provide dentistry services to SHI-insured persons in need of inpatient long-term care. The calculation of the utilization rates will be carried out the same way as with the Zi data. The key figures will be calculated for the entire target population as well as stratified according to age group (5-year age brackets up to age 95 years and older), sex, and reporting year. The utilization from 2016 to 2020 will be presented chronologically. When implementing the described claims data analysis, we will follow the guidelines of Good Practice of Secondary Data Analysis [23].

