## Discussion

### Principal Findings

This study will provide current and reliable data on the utilization of preventive services in the 55-plus age group in Saxony-Anhalt. It will provide knowledge about the determinants, reasons, and barriers associated with their use and thereby make it possible to derive prevention recommendations for the target population. Moreover, the search for information about this topic and the subsequent systematic evaluation thereof sheds light on the information available and the quality of the material. The findings can be used by actors in the social and health sectors (eg, physicians, health insurances) for target group–specific evaluation and for further development of the existing range of information and preventive services offered.

With the differentiated methodical approaches, multifaceted knowledge about the use of preventive services in old age can be generated. The mixed methods design offers the potential to gain a comprehensive understanding of the utilization of preventive services. The strengths of the methods can synergistically complement each other and compensate for limitations. The regional focus in the analysis of the Zi data makes it possible to identify the extent of regional variations in the utilization of preventive services in Saxony-Anhalt. These empirical findings can serve as the basis for deriving strategies to reduce that variation. Furthermore, the study takes into account different perspectives and views of residents and relevant stakeholders, which is essential for the identification of further potential for prevention. In the semistructured interviews and in the survey of residents, we capture the perspectives of the target group. These insights are complemented by the experiences of physicians by means of the focus group discussions. There are continual discussions with the regional cooperation partners about, for example, the feasibility of the study and the development of prevention recommendations. The results of the study are primarily relevant for the federal state of Saxony-Anhalt. They are potentially transferable to other structurally weak regions in other federal states that are strongly affected by demographic change.

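### No age-sex-standardized rate is named for the state-versus-Germany, district and time-trend comparisons of claims data, so differences in age and sex mix can appear as differences in use

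*Protocol article*

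**What the plan says.** The Claims Data Analysis section of the protocol article gives the rate in full. The numerator is "the number of insured people who have made use of a certain service at least once within a defined reporting period" and the result is "divided by the population eligible for the respective service among those with SHI". No weights and no standard population are mentioned.

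Three comparisons rest on this rate:

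- State against nation: "the utilization rate in Saxony-Anhalt will be compared with the rate for the entire German federal territory".
- Within the state: "Regional differences in Saxony-Anhalt will be examined at the district and urban district levels".
- Over time: a chronological presentation from 2011 to 2020. For the dental data it runs from 2016 to 2020, with rates calculated as for the Zi data.

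On presentation, the section says: "The key epidemiological figures will be shown for the entire target population and stratified according to age group", with "5-year age brackets up to age 95 years and older), sex, region, and reporting year as well as other characteristics". The dental figures are to be stratified by age group, sex and reporting year, but not by region.

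Standardization or age-sex adjustment is mentioned nowhere in the article.

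**The concern.** The article itself supplies the reasons why age mix matters. The Background section says that use of preventive services differs by sex and age, among other factors, and describes Saxony-Anhalt as strongly affected by demographic change. It also reports very high East German birth numbers from 1959 to 1968. Part of that cohort reaches age 55 inside the reporting window, so the age mix of the 55-plus denominator can be expected to change while the trend is being measured.

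An unweighted rate over everyone aged 55 and older combines two things: how much people of a given age and sex use the service, and how many people of each age and sex there are. Two districts with identical use at every age can have different overall rates.

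The Principal Findings section says of the regional variation: "These empirical findings can serve as the basis for deriving strategies to reduce that variation". Variation that comes from age mix is not something a prevention strategy can reduce, so a district could be singled out, or overlooked, for its demography.

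**Working it through.** The article states no rate comparison, sample size or power figure for the claims data, so there is no stated figure to reproduce. The check is of the mechanism and its plausible size.

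**Exposure of the trend.** The birth years 1959 to 1968 come from the Background section.
- The 1959 cohort turns 55 in 1959 + 55 = 2014.
- The 1965 cohort turns 55 in 1965 + 55 = 2020.
- So the 1959 to 1965 cohorts enter the 55-plus group within 2011 to 2020. For the dental window, the cohorts that enter are those of 2016 − 55 = 1961 to 2020 − 55 = 1965.

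**Formula.** Let areas (or years) A and B have the same age-specific rates. Then

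crude difference = Σ over age bands of (share in A − share in B) × common rate.

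With only two bands differing, this is (difference in older share) × (older rate − younger rate). Direct standardization gives 0 by construction, because both areas receive the same weights.

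**Two-band illustration.** All inputs are assumed; the article gives neither age shares within 55-plus nor age-specific rates. With a 30-point gap in use:
- 3-point shift: 0.03 × 30 = 0.9 points.
- 5-point shift: 0.05 × 30 = 1.5 points.
- 8-point shift: 0.08 × 30 = 2.4 points.

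Over a wider grid of assumptions:

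| Difference in older share | Gap of 5 points | Gap of 40 points |
|---|---|---|
| 1 point | 0.05 | 0.4 |
| 3 points | 0.15 | 1.2 |
| 5 points | 0.25 | 2.0 |
| 10 points | 0.5 | 4.0 |

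**Nine-band illustration** (55-59 to 95 and older, inputs again assumed). Area A has 3 points fewer people aged 55-59 than area B, and 1 point more in each of 65-69, 75-79 and 80-84.
- Service whose use rises with age (rates 15% at 55-59, then 40%, 53% and 57% in the three older bands): −0.03 × 15 + 0.01 × (40 + 53 + 57) = −0.45 + 1.50 = +1.05 points (40.99% against 39.94%).
- Service whose use falls with age (rates 30%, then 28%, 22% and 15%): −0.03 × 30 + 0.01 × (28 + 22 + 15) = −0.90 + 0.65 = −0.25 points (23.07% against 23.32%).

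The same age difference thus makes one area look better on one service and worse on another, although use at each age is identical.

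**The case against.** The strongest case against is that the article never says the comparisons are crude. It writes only of the utilization rate, and the same paragraph plans 5-year age and sex strata, which are a recognized way to remove composition. The denominator is limited to people eligible for each service, which already takes out part of the age and sex difference. The article is condensed, commits to good-practice guidelines for secondary data, and may leave the choice of standard population to a fuller plan.

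Much of this stands. A reader might infer that the plan commits to crude comparisons only, or that age structure will distort the results. The text supports neither: a crude comparison is the natural reading of the defined rate, not an explicit statement, and the distortion is possible rather than shown. A reader might also take the Background figure, "the proportion of the population of Saxony-Anhalt aged 65 years and older was approximately 27% of the total population", as proof that the state's 55-plus group is older than Germany's. It is not. It is a share of the total population, has no national figure beside it, and says nothing about the mix within 55-plus.

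What does not dispose of the point is this. The article does fix an estimator, without weights, and names the comparisons to be made with it. Strata shown beside an overall rate provide no age-comparable summary: nine age bands by two sexes, for each service, district and year, need a weighting rule before districts or years can be compared as a whole. Restricting to the eligible removes ineligible people but does not equalize ages among those who remain. Nor does the article say that the strata are cross-classified. Because the Limitations section states that only aggregated data are provided, a missing cross-classification could not be rebuilt from individual records.

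**Conclusion.** The point holds as a gap in the stated estimator. The rate as defined is unweighted, it is to be compared between state and nation, between districts and over time, and no age-sex-standardized summary is named. Differences in age and sex mix among the eligible can therefore appear as differences in use, in results that the article wants to use for strategy.

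The real size cannot be determined from the article. The 0.9 to 2.4 points rest on an assumed 3 to 8 point shift in age share, an assumed 30-point gap in use, and identical age-specific use in the populations compared. Smaller or larger assumptions give about 0.05 to 4 points. The direction depends on whether use of the service rises or falls with age. If the comparisons are in fact made within jointly defined age-sex strata, or standardized under a fuller plan, the bias does not arise and only the wording needs to change.

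**What to change.** Add to the Claims Data Analysis section that the state-versus-national, district and trend comparisons, including the dental time series, are based on rates directly standardized by 5-year age band and sex. Use one fixed reference population, applied within each service's eligible group, for example the German SHI-insured population aged 55 and older in one named reference year. Report the crude rates alongside, since they remain useful for service planning.

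Confirm with the data holders that the aggregates are delivered cross-classified: age band by sex by region by year for the Zi data, and age band by sex by year for the dental data.

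The cost is a short addition to the text and slight extra analysis. If the cells are not already cross-classified, an adjusted data request is also needed. The article describes the data as still being prepared, with delivery expected in January 2022, so this is best settled before delivery.
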